## Methods

### Design and study setting

The current study is an observational study within four primary schools located in Holendrecht, Amsterdam. Holendrecht is a neighborhood in the south eastern part of Amsterdam. Since the intervention is innovative and is being developed during the intervention period, we have chosen for this mixed-methods observational design. Stadsscholen020 is a new and complex intervention approach that comprises multiple interacting components and therefore we aim to evaluate policy, practice, and the implementation directly from the start of the intervention. Based on the mixed-methods design, our current study can be divided into three slightly overlapping and complementary study parts. First, we will conduct a longitudinal study (Part I) to evaluate the effects on the individual level for children using five assessment points. Second, in a cross-sectional study (Part II) we will evaluate the effects on school and neighborhood level. Third, using a process evaluation (Part III) we will study the implementation of the intervention and interpret our findings of the other study parts. For each study part different methods and instruments are used with regards to the data collection.

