### Eligibility criteria

In the initial pilot year (2015–2016) only four primary schools in Amsterdam Holendrecht neighborhood were focus of Stadsscholen020. Currently, eight other schools from deprived neighborhoods in Amsterdam are involved. The so called ‘Stadsscholen’ are selected based on their increased risk for educational disadvantages due to challenges and difficulties on family and neighborhood level (based on unpublished data from the municipality). Although there are more schools involved in the Stadsscholen020 program, for this research study we have chosen to focus on the four schools in the neighborhood Holendrecht since the interdisciplinary approach initially started at these schools. Because interdisciplinary approaches are time-consuming to implement in a school setting and it takes time to observe the potential effects, we have chosen for the schools with the longest intervention period. Also, our decision to focus on the four schools is based on considerations to limit the complexity of our study and conduct an in-depth process evaluation within the time frame of our study.

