#### Part II. Cross-sectional study

Complementary to the individual data and detailed information from the longitudinal and process evaluation, the cross-sectional study will include data from public databases of the municipality of Amsterdam (Onderzoek, Informatie en Statistiek, OIS), the Public Health Service of Amsterdam (GGD), and The Education Executive Agency of the Dutch Ministry of Education, Culture, and Science (Dienst Uitvoering Onderwijs, DUO). These data will be used to observe the effects of Stadsscholen020 during the intervention period on determinants related to health, poverty, and academic achievement that are available on school and neighborhood level. Data from the schools and the neighborhood where the schools are located (Amsterdam Holendrecht) will be compared with data on a wider district and city level. Table 2 shows the overview of the indicators related to the primary and secondary outcomes that will be examined in this cross-sectional study.

**Table 2 Tab2:** Overview of primary and secondary outcomes, indicators, and measurements

	Informants	Study parts		
		Longitudinal study *5 assessments*	Cross-sectional study *5 year period*	Process evaluation *5 assessments*
*Child Health*				
Life satisfaction (Cantril Ladder)	Child	×	×	
Socioemotional Well-being (SDQ)	Child	×		
Quality of life (KIDSCREEN)	Child	×		
Sport club membership	Child	×		
Dietary behavior (daily warm meal and fruit intake questions)	Child	×		
% 5-years old / 10-years old children with overweight (including obesity)	GGD		×	
% 5-years old / 10-years old children having breakfast every day	GGD		×	
% 5-years old / 10-years old children eating greens every day	GGD		×	
% 5-years old / 10-years old children that is physical active	GGD		×	
% Households supported by child welfare organizations (OKT)	GGD		×	
*Child Poverty*				
Family Affluence (FAS)	Child	×		
Stadspas ownership (minimal income permit)	Child	×		
% Households depending on social security benefits	OIS		×	
% Households having an income up to 120% of the social minimum	OIS		×	
% Children having parents with a lower education	OIS		×	
*Child Academic Achievement*				
Secondary school qualifications	DUO		×	
School test results (CITO)	DUO		×	
*School Environment*				
Teacher self-efficacy (TSES)	Teacher			×
Classroom climate (Class climate scale)	Teacher			×
School and neighborhood safety (additional questions)	Child			×
Bullying (KIDSCREEN and additional questions)	Child			×

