#### Data analysis

To investigate whether the Stadsscholen020 program leads to significant changes on primary and secondary outcomes over time, repeated measures ANOVAs and linear mixed models analysis techniques will be performed for this the longitudinal data. The linear mixed models technique is able the handle missing data using a likelihood based approach, every observation for every participant is used, irrespective of their missing data. The appropriate covariance structure, which accounts for the within-subject correlation, will be chosen based on the model fit using the − 2 log likelihood value. Cross-sectional data will be analysed by comparing means between the different levels (school, neighbourhood, district, and city level) using independent *t*-tests and ANOVA.

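### Part II is meant to show programme effects, but its only stated analysis compares levels between areas, with no before-after or level-by-time contrast

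*Protocol article*

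**What the plan says.** The article gives Part II an evaluative purpose twice. Under Design and study setting: "in a cross-sectional study (Part II) we will evaluate the effects on school and neighborhood level". Under Part II. Cross-sectional study: "These data will be used to observe the effects of Stadsscholen020 during the intervention period on determinants related to health, poverty, and academic achievement". There, data for the schools and for Holendrecht "will be compared with data on a wider district and city level".

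The analysis is one sentence under Data analysis: "Cross-sectional data will be analysed by comparing means between the different levels (school, neighbourhood, district, and city level"), "using independent *t*-tests and ANOVA". The sentences just before it do specify change over time, by repeated measures ANOVA and linear mixed models, but only for the longitudinal data of Part I.

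Three other statements bear on the point:

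- Eligibility criteria: the programme schools "are selected based on their increased risk for educational disadvantages due to challenges and difficulties on family and neighborhood level".
- Table 2 gives Part II a five-year period, without dating it.
- Intervention: the programme runs for two school years, September 2016 to July 2018, after a pilot in 2015–2016.

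**The concern.** A comparison of levels asks whether Holendrecht or its schools differ from district and city. The stated aim asks whether the programme changed anything. The two questions coincide only if the areas were alike beforehand, and the selection rule makes that implausible. A significant level difference would then reflect deprivation that was there before the programme, and a non-significant one could mean either no gap or a gap that the programme had closed.

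Part II is the only part with an external reference. In Table 2 it alone carries the direct achievement outcomes (CITO results and secondary school qualifications), which belong to a named secondary outcome. It also holds the overweight, breakfast, greens and physical activity indicators listed under child health, the primary outcome. If its one stated contrast cannot answer the question, these outcomes have no usable effect estimate.

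**Working it through.** The article gives no sample size, effect size or power for Part II, so there is no figure of the plan to reproduce. The check compares what each contrast estimates and then illustrates the size under assumptions.

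**What each contrast estimates.** Let g be the starting gap (Holendrecht worse than the reference by g) and e the true gain in the programme years, with the reference unchanged.

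- Level difference in a programme year: −g + e. It is zero when e = g, and negative whenever e < g.
- Change in the gap, before to after: (−g + e) − (−g) = e. The starting gap cancels.

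**Illustration 1: level test in a programme year.** Assumptions: 477 children on the programme side (the total at the four schools under Power calculation), 5,000 in the reference, outcome in SD units, two-sided α = 0.05, independent samples before and after.

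SE of level difference = √(1/477 + 1/5000) = 0.0479. SE of change in gap = √2 × 0.0479 = 0.0678.

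Example with g = 0.2, e = 0.1: level z = −0.1/0.0479 = −2.09, so P(significantly worse) = Φ(2.09 − 1.96) = 0.55. Change z = 0.1/0.0678 = 1.48, so P(significantly better) = Φ(1.48 − 1.96) = 0.31.

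| g (SD) | e (SD) | Level test: worse | Level test: better | Change in gap: better |
|---|---|---|---|---|
| 0.1 | 0 | 0.55 | 0.00 | 0.025 |
| 0.1 | 0.2 | 0.00 | 0.55 | 0.84 |
| 0.2 | 0 | 0.99 | 0.00 | 0.025 |
| 0.2 | 0.1 | 0.55 | 0.00 | 0.31 |
| 0.2 | 0.2 | 0.025 | 0.025 | 0.84 |
| 0.3 | 0.1 | 0.99 | 0.00 | 0.31 |
| 0.3 | 0.2 | 0.55 | 0.00 | 0.84 |
| 0.5 | 0.2 | 1.00 | 0.00 | 0.84 |

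The level result is driven by g − e; the change-in-gap result depends on e only. The second row shows that a gain larger than the gap does appear as better.

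**Illustration 2: five yearly percentages per level, pooled.** Pooling is an assumption; the article does not state it. Further assumptions: 119 children per year on the programme side (477/4, a count for the four schools and not for Holendrecht), 8,000 in the city, city level 20%, three unexposed and two programme years, equal-variance t-test of five against five values, 20,000 simulated series.

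- No effect, stable gap of 3, 5, 8 or 10 points: significantly worse in 36%, about 70%, 96% and 99%. The change-in-gap test rejects in about 5%.
- Gap 10, gain 10: the pooled difference is 10 − 10 × 2/5 = 6 points worse, significant in 37%. The change in the gap is estimated at −10 points, power about 79%.
- Gap 10, gain 5: worse in about 90%; power for the change about 28%.
- Gap 5, gain 5: worse in about 24%; power for the change about 30%.
- Gap 10, gain 3: power for the change about 13%.

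**Price in precision.** With s the standard error of one year's gap, the five-year level difference has SE s/√5 = 0.447s. The change has SE s√(1/3 + 1/2) = 0.913s with three unexposed years, or s√(1/2 + 1/2) = s with two. The ratios are 2.04 and 2.24. At a 5-point gap, s = √(0.25 × 0.75/119 + 0.20 × 0.80/8000) = 4.0 points, so the SE is 3.6 to 4.0 points against 1.8.

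**The case against.** The strongest reply is that one condensed sentence is being read too hard. The article nowhere says that a level difference will be called an effect. It describes Part II as complementary, gives it five years of data, and concedes in the Discussion that causal relationships are difficult to determine without randomisation. Levels might be compared year by year. Part I, not Part II, tests the individual-level primary outcome over time.

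Several of these points stand as limits. A reader might infer that the authors will report the deprivation gap as a programme effect; the documents support only that the stated test cannot separate the two. A reader might infer that the test rejects whatever the programme does, or that a helpful programme would usually look worse than the city. Neither is supported: at a 3-point gap with no effect the illustration rejects in 36%, with gap and gain both 10 points it shows worse in 37%, and the true gap is unknown. The only relevant value given is that 27% of Holendrecht households have an income up to 120% of the social minimum, with no matching district or city figure. The dilution to two fifths applies only if five years are pooled, which is not stated. Nor do the documents show that the whole neighbourhood is exposed, since the programme acts through four schools.

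The core is untouched. A year-by-year comparison of levels is still a comparison of levels unless a contrast between years is specified. The general caveat on causality does not mention the gap created by selection. This is a method that the article states, not a detail left to a fuller plan.

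**Conclusion.** The point holds as a mismatch between aim and test. Part II is to evaluate effects, its stated analysis contains no before-after or level-by-time contrast, and the schools were selected for disadvantage. A level difference is therefore expected without any effect, and a gain smaller than the starting gap can still appear as worse than the city.

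The direction follows from the documents alone. The size does not: every percentage above is an illustration under assumed gaps, sample sizes and variances, and those in the second illustration also assume pooling. What does not depend on the size of the gap is that, in a level comparison, gap and effect enter only as their difference, whereas the gap cancels in the change. Reading that change as a programme effect in turn assumes that the gap would otherwise have stayed stable.

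**What to change.** In Data analysis, replace the Part II sentence with these provisions:

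- For each indicator with pre-programme values, the effect estimate is the change in the gap between the study schools (or Holendrecht) and the district or city reference, from pre-programme years to school years 2016–17 and 2017–18, as a level-by-period interaction or difference-in-differences with its confidence interval.
- Level differences, and indicators without pre-programme values, are reported as description only.
- The five-year window is dated so that it includes pre-programme years, and the pilot year 2015–16 is shown separately.
- Where the databases allow, Holendrecht and the other programme schools are excluded from the reference. The city contains Holendrecht, and eight other Amsterdam schools are also in the programme.

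The sources are the public databases already named, and a five-year period is already planned. Whether they hold comparable pre-programme values for every indicator and level cannot be seen from the article and must be checked. The price is a clearly wider interval, about double the standard error of a five-year level difference in the illustration, and low power for small changes (about 28% for 5 points and 13% for 3 points from a 10-point gap). A null change in the gap should therefore be reported with its interval and not as absence of effect.

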## Discussion

To promote equal chances of children growing up in deprived neighborhoods and to decrease long-term consequences of poverty the municipality of Amsterdam initiated a school-based interdisciplinary intervention (Stadsscholen020). The current study aims to evaluate this intervention program at four primary schools in a deprived neighborhood. The implementation of a school-based interdisciplinary approach via primary schools combining the cross-sectoral domains health, poverty, and academic achievement is innovative and the knowledge about the effectiveness is currently limited. Research on this complex intervention approach contributes to more insights on effective ways to decrease inequalities of children growing up in poverty. Using a mixed-methods design among three study parts we intent to examine the potential benefits of the intervention on a variety of outcome measures. Conducting a study in a multi-ethnic sample is a strength of our study and an important step forward in intervention research since these populations are difficult to include as participants in research studies. Another strength of the current study is including a process evaluation. Since, the evaluation focuses on a complex intervention and the current study lacks randomization of the participating schools, causal relationships between interventions and outcomes are difficult to determine. The process evaluation will contribute to these methodological limitation in order to interpreted our findings on the outcome measures and will provide more detailed knowledge about the implementation processes.

However, this study has a number of other limitations which may threaten to value and validity of our study. First, a potential limitation of our study is the large variety of activities and interventions that take place at the schools during the Stadsscholen020 intervention period. It will be a challenge to describe all these activities and interventions into sufficient detail and to monitor the implementation of them separately. Because an interdisciplinary approach can be hampered by the absence of an interdisciplinary or inter-sectoral focus and lack of communication between parties. Therefore, the process evaluation and a close collaboration with the practice and policy stakeholders is important to help us addressing these concerns and to identify strengths and barriers in the implementation process. In order to identify successful components of the interdisciplinary approach, we will describe what is happening at the schools as detailed as possible. Second, since the ethnic composition of the population in the neighborhood is very specific, this can affect the generalizability of our findings to other populations and neighborhoods. Third, a limitation often present in research on complex and interdisciplinary interventions is that the time period of our research project may be too short. Yet, we do not know how long it takes to observe significant changes on the child outcomes. Therefore, it is possible that Stadscholen020 leads to changes on the longer term, that are not already manifested during the time frame of our research project. Despite these limitations, study outcomes are informative to both policy and practice aimed at minimizing unequal chances of children growing up in deprived neighborhoods and help them to start a successful academic career early in their lives.

## Abbreviations

CITO: Centrale Eindtoets Basisonderwijs (Final Examination for Primary Education)
DUO: Dienst Uitvoering Onderwijs (The Education Executive Agency)
FAS: Family Affluence Scale
GGD: Public Health Service of Amsterdam
OIS: Department of Research, Information, and Statistics of the municipality of Amsterdam
OKT: ouder-kind team (parent-child team)
SDQ: Strengths and Difficulties Questionnaire
TSES: Teacher Sense of Efficacy Scale
